**11.2. General Principles**

The efficacy report of this study, including both primary and secondary efficacy endpoints, will be based on the Intention-To-Treat (ITT) principle. The analysis strategies are as follows:

1. Quantitative variables will be described using mean (standard deviation), median (minimum, maximum, or interquartile range). Categorical variables will be presented as counts (percentages).
2. All statistical tests will be two-sided. A p-value ≤ 0.05 will be considered statistically significant.
3. Enrollment and Completion Status

The number of enrolled and completed cases will be summarized, and a list of dropout cases will be provided. The total dropout rates between groups will be compared using the chi-square test.

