4.3.2. Post-enrollment Observation Indicators

1. Specific indicators after enrollment (see Table 1):
   - Vital signs and comprehensive physical examination;
   - Routine tests: CBC, urinalysis, blood biochemistry, ECG, fingertip oxygen saturation, tumor markers, IL-6 and IL-10 levels, peripheral blood immune cell function, lymphocyte subpopulations;
   - Pulmonary function tests: percentage predicted of DLco, FVC, and DLCO/VA;
   - Six-minute walk test (graded and distance);
   - SGRQ;
   - LCQ;
   - mMRC Dyspnea Scale;
   - Chest HRCT;
   - Acute exacerbation events (frequency and severity).
2. Adverse events during the administration period of the investigational drug. If any adverse event occurs, the patient will be followed up until resolution or end of treatment. The occurrence time and severity of complications involving various organ systems (e.g., cardiac events, cerebrovascular events, infections, etc.) will be recorded;
3. For participants discharged or deceased after enrollment, record the death event, length of hospital stay, duration of mechanical ventilation, and total treatment cost;
4. Long-term observation indicators post-enrollment (up to 1 year):
   Considering the long-term safety concerns of exosome therapy, follow-up calls will be conducted at weeks 24 and 48 to record any adverse events for long-term safety assessment.

(see next page for Table 1)

Table 1. Schedule of Assessments

| Visit | Screening  -2d～0d | Baseline  D0 | D1 | D2 | D3 | D4 | D5 | D6 | D7 | D8 | D28  ±3d | D84  ±3d | D180  ±5d | D360  ±7d |
| --- | --- | --- | --- | --- | --- | --- | --- | --- | --- | --- | --- | --- | --- | --- |
| **Basic medical history** | | |  |  |  |  |  |  |  |  |  |  |  |  |
| informed consent | × |  |  |  |  |  |  |  |  |  |  |  |  |  |
| Demographic data | × |  |  |  |  |  |  |  |  |  |  |  |  |  |
| General clinical data | × |  |  |  |  |  |  |  |  |  | × | × |  |  |
| **Security assessment** | | |  |  |  |  |  |  |  |  |  |  |  |  |
| Vital sign | × | × | × | × | × | × | × | × | × | × | × | × |  |  |
| Physical examination | × | × | × | × | × | × | × | × | × | × | × | × |  |  |
| Blood routine examination |  | × |  |  |  |  |  |  |  | × |  | × |  |  |
| urinalysis |  | × |  |  |  |  |  |  |  | × |  | × |  |  |
| Urine pregnancy test (women of gestational age only) |  | × |  |  |  |  |  |  |  | × |  | × |  |  |
| Infectious disease screening |  | × |  |  |  |  |  |  |  |  |  | × |  |  |

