**5.3. Criteria for Early Withdrawal**

Subjects will be withdrawn from the study if they request to discontinue participation or withdraw informed consent (e.g., due to poor efficacy or adverse events), or are unable to comply with study requirements. Subjects may also be withdrawn at the discretion of the investigator if serious complications or comorbidities, or severe adverse events occur.

The reason for withdrawal must be thoroughly documented. The most recent major efficacy assessment before withdrawal will be used as the final result for statistical analysis. The subject’s CRF (Case Report Form) must be retained for future reference.

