# 8 Criteria for Suspension and Termination of the Clinical Study

**8.1. Criteria for Participant Withdrawal or Study Termination**

1. The subject withdraws informed consent and requests to discontinue participation.
2. The subject exhibits significant non-compliance.
3. Occurrence of pregnancy, serious adverse events, death, or loss to follow-up.
4. Use of prohibited concomitant medications.
5. The subject fails to attend scheduled visits.
6. Investigators should make every effort to ensure that each subject completes the follow-up phase, unless discontinuation is clearly in the subject's best interest. Subjects who withdraw from the study should still enter the follow-up phase and will receive periodic follow-ups to monitor survival status until death or the end of the study.

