**11.4. Efficacy Evaluation**

(1) Primary Efficacy Evaluation:

The proportion of patients who experienced disease progression events within 84 days after enrollment or by the end of follow-up will be calculated and compared between groups using the chi-square test.

(2) Secondary Efficacy Evaluation:

Proportions of individual disease progression events will be compared using chi-square or Fisher's exact tests. Time to disease recovery and symptom improvement will be analyzed using grouped t-tests or Wilcoxon rank-sum tests.

(3) Other Observational Indicators:

Changes in IL-6 levels post treatment will be compared between groups using repeated measures analysis. Comparisons at different time points will be made using t-tests. Quality of life scores and total hospitalization costs will also be compared using t-tests or Wilcoxon rank-sum tests.

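### Death is classed with withdrawal and not exempted from the last-assessment rule, and disease-caused deaths have no assured comparison by arm although they are recorded.

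*Protocol*

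**What the plan says.** **Withdrawal.** Protocol 8.1, item 3, gives as one criterion for participant withdrawal or study termination: "Occurrence of pregnancy, serious adverse events, death, or loss to follow-up". Item 6 keeps withdrawn patients in follow-up for survival status.

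**Value used after withdrawal.** Section 5.3 states: "The most recent major efficacy assessment before withdrawal will be used as the final result for statistical analysis". Its own reasons are the patient's request, withdrawn consent, inability to comply, and investigator discretion: "Subjects may also be withdrawn at the discretion of the investigator if serious complications or comorbidities, or severe adverse events occur". Death is not named there, and it is not exempted.

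**Disposition.** Section 11.2(3) says "The number of enrolled and completed cases will be summarized, and a list of dropout cases will be provided", followed by "The total dropout rates between groups will be compared using the chi-square test". There is no separate category for death.

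**Data collected.** Section 4.3.2(3) says: "For participants discharged or deceased after enrollment, record the death event, length of hospital stay, duration of mechanical ventilation, and total treatment cost".

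**Efficacy.** Section 11.4(1) compares "The proportion of patients who experienced disease progression events within 84 days after enrollment", or by the end of follow-up. The term for these events is not defined and death is not mentioned. Section 11.4(3) compares quality-of-life scores by t-test or Wilcoxon test.

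**Safety.** Section 10.4 counts a death as an SAE only if the underlying disease or its complications did not directly cause it. Section 10.1 leaves worsening of the treated disease out of the exacerbations collected as AEs. Section 11.5 summarizes AEs and SAEs by treatment group, but on a safety set that 11.1 limits to randomized patients who received at least one vesicle dose.

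**The concern.** Death is an outcome, and a different kind of event from a missed visit or a refusal. If it follows the withdrawal route, two things can go wrong. A patient who dies after a good early visit can enter the quality-of-life comparison with that visit's score as the final result. The death can also sit inside a dropout total where ordinary withdrawals in the other arm offset it.

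The other places where a death might surface do not close the gap when the lung disease is the cause: the SAE definition excludes it, and the progression endpoint does not clearly include it. Safety is the primary objective (section 2.1), so deaths by arm should not depend on how several sections happen to be read.

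**Working it through.** The protocol states no mortality, dropout or progression rate and no power, so there is no figure to reproduce beyond 12 + 12 = 24 (section 6). The check is a trace through the text, followed by illustrations on assumed counts.

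**1. Where a death would appear, section by section**

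| Place | Death caused by the disease | Death not caused by the disease |
|---|---|---|
| 8.1(3) | Withdrawal criterion | Withdrawal criterion |
| 11.2(3) | Not a completer; dropout on the natural reading | Same |
| 10.4 and 11.5 | Excluded from SAEs | SAE, summarized descriptively |
| 11.1 safety set | Vesicle recipients only, as worded | Same |
| 11.4(1) | Unclear, events undefined | Unclear, events undefined |
| 11.4(3), quality of life | Pre-death score, if 5.3 applies | Same |

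The left-hand column contains no entry that assures a comparison by arm.

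**2. Window for a carried-forward score.** Table 1 schedules SGRQ and LCQ at baseline, Day 8, Day 28 and Day 84. Only a death before the Day 84 visit can leave an earlier score as final. A death between Day 28 and Day 84, for example, would leave the Day 28 score.

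**3. Weight of one patient.** With 12 per arm, one death is 1/12 = 8.3 percentage points of a proportion and 8.3% of the weight in an arm mean. Two deaths are 2/12 = 16.7 points.

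**4. Masking in the dropout total (assumed counts).** Suppose one arm has 3 deaths and no other withdrawals, and the other has 3 ordinary withdrawals and no deaths.
- Pooled dropout: 3/12 vs 3/12, chi-square p = 1.00.
- Deaths alone: 3/12 vs 0/12. Fisher exact two-sided p = 2 × C(12,3)/C(24,3) = 2 × 220/2024 = 0.217. Uncorrected chi-square = 24 × (3 × 12 − 0 × 9)² / (12 × 12 × 3 × 21) = 3.43, p = 0.064.

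**5. What a separate test could show (assumed counts)**

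| Deaths, 12 per arm | Fisher p | Uncorrected chi-square p |
|---|---|---|
| 2 vs 0 | 0.478 | 0.140 |
| 3 vs 0 | 0.217 | 0.064 |
| 4 vs 0 | 0.093 | 0.028 |
| 5 vs 0 | 0.037 | 0.012 |

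By Fisher's test, with no deaths in the other arm, five are needed to reach the 0.05 level of 11.2. What is gained by separating deaths is that they can be seen by arm. Power is low either way.

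**6. Chance that the question arises.** If each patient's risk of death during follow-up is r, P(at least one among 24) = 1 − (1 − r)^24. For assumed r of 1%, 2% and 5% this is 0.21, 0.38 and 0.71. These risks are not in the protocol, and they refer to follow-up as a whole. The chance of a death before Day 84 would be smaller.

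**The case against.** A reader might infer that the protocol counts every death as a dropout, always keeps a pre-death value, and lets deaths show nowhere but in the dropout total. The documents do not go that far:
- Dropout is undefined in 11.2(3). The last-assessment rule sits in 5.3, whose list omits death, while 8.1 has no such rule. The combined effect comes from joining three sections. It is the natural reading, because 8.1 calls death a withdrawal criterion and nothing exempts it, but it is not stated.
- Deaths not caused by the disease would appear in the SAE summary. Section 5.3 requires reasons for withdrawal to be documented and 11.2(3) requires a list of dropouts, so individual deaths could be traced.
- The progression events in 11.4(1) are undefined and might be meant to include fatal progression.
- Section 11.5 speaks of treatment groups, which suggests that placebo patients were meant to be in the safety set despite the wording of 11.1.

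A reader might also infer that efficacy is biased toward the arm with more deaths. That would require unequal deaths before Day 84 with the 5.3 rule applied to them. Section 11.4 names no between-arm test of lung function or walk distance, so of the scheduled scores only quality of life is clearly exposed.

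A table of deaths by arm may also sit in an analysis plan that is not shown. Its absence here would not be a finding by itself.

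All of this limits the claim. What remains rests on statements the protocol does make: the classification in 8.1, the unqualified rule in 5.3, the exclusion in 10.4 and the safety-set wording in 11.1.

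**Conclusion.** The point stands as a defect of wording with a real consequence. Followed as written, a disease-caused death meets a withdrawal criterion, is excluded from SAEs, is not assured of counting as progression, and can leave a favourable earlier quality-of-life score as the final result. No section guarantees that such deaths are compared by arm, although deaths and survival status are both collected.

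The size is conditional. It is zero if nobody dies, and 8.3 percentage points of an arm for each death otherwise. The carried-forward score matters only for deaths before Day 84. The conclusion assumes that the 5.3 rule reaches withdrawals under 8.1 and that a death counts as a dropout in 11.2(3). Both are the natural reading and neither is explicit. The counts of deaths and the 1% to 5% risks are illustrations only. Correction is advisable because it costs little and deaths bear on the primary objective.

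**What to change.** 1. **11.2(3):** report deaths as their own disposition category, separate from dropouts, and leave them out of the compared dropout rate.
2. **5.3:** limit the last-assessment rule to withdrawals other than death, and state, here or in the analysis plan, how a patient who died enters the quality-of-life comparison.
3. **11.4(1):** state that death from any cause by Day 84 counts as an event in the proportion, and show cause of death alongside.
4. **11.5:** tabulate all-cause deaths by randomized arm in all randomized patients (the full analysis set, not the safety set as worded) to Day 84 and to Day 360, the last contact in Table 1. Present this descriptively, since 12 per arm does not support a powered mortality test.

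The cost is a few sentences and one table from data already collected under 4.3.2(3) and 8.1(6). The downside is small: a death unrelated to the lung disease also counts as an event in 11.4(1), which is why its cause should be shown. No change to treatment or follow-up is involved.

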**11.3. General and Baseline Characteristics**

(1) Demographic information, prior medication history, and comorbidities will be descriptively summarized.

(2) For quantitative variables like age, baseline comparisons between groups will be performed using grouped t-tests or Wilcoxon rank-sum tests, depending on the characteristics of the variables. For categorical variables like gender or comorbidities, comparisons will be made using chi-square or Fisher's exact tests.

**11.4. Efficacy Evaluation**

(1) Primary Efficacy Evaluation:

The proportion of patients who experienced disease progression events within 84 days after enrollment or by the end of follow-up will be calculated and compared between groups using the chi-square test.

(2) Secondary Efficacy Evaluation:

Proportions of individual disease progression events will be compared using chi-square or Fisher's exact tests. Time to disease recovery and symptom improvement will be analyzed using grouped t-tests or Wilcoxon rank-sum tests.

(3) Other Observational Indicators:

Changes in IL-6 levels post treatment will be compared between groups using repeated measures analysis. Comparisons at different time points will be made using t-tests. Quality of life scores and total hospitalization costs will also be compared using t-tests or Wilcoxon rank-sum tests.

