**2.2. Secondary Objectives**

1. to evaluate changes from baseline in pulmonary function on Days 4 and 8, Week 4, and Week 12;
2. to assess HRCT imaging changes from baseline at Week 4 and Week 12;
3. to evaluate changes from baseline in six-minute walk distance (graded and actual distance) on Days 4 and 8, Week 4, and Week 12 for patients meeting criterion 5.1.2 (2) for HRCT-defined fibrotic lesions;
4. to assess changes from baseline in the St. George’s Respiratory Questionnaire (SGRQ) on Days 4 and 8, Week 4, and Week 12;
5. to assess changes from baseline in the Leicester Cough Questionnaire on Days 4 and 8, Week 4, and Week 12;
6. to assess changes from baseline in the modified Medical Research Council (mMRC) Dyspnea Scale on Days 4 and 8, Week 4, and Week 12;
7. to monitor the frequency and severity of acute exacerbations in patients with HRCT-defined pulmonary fibrotic lesions from Days 1–8, Week 4, and Week 12.

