# 9. Efficacy Evaluation Criteria

**9.1. Efficacy Assessment**

(1) Primary Efficacy Endpoints

- Clinical symptoms and signs
- Pulmonary function
- High-resolution chest CT (HRCT)
- Frequency and severity of acute exacerbation events

(2) Secondary Endpoints

- 6-minute walk distance (6MWD), including grade and distance
- St. George's Respiratory Questionnaire (SGRQ)
- Leicester Cough Questionnaire
- Modified Medical Research Council Dyspnea Scale (mMRC)

(3) Other Observational Indicators

- Post-treatment changes in IL-6 levels, peripheral blood immune cell function, and peripheral blood lymphocyte subsets.

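### The secondary efficacy analysis in Protocol 11.4(2) tests undefined progression and recovery outcomes and names none of the four secondary endpoints in 9.1(2)

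*Protocol*

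**What the plan says.** Protocol 9.1(2) lists the secondary endpoints as "6-minute walk distance (6MWD), including grade and distance", the SGRQ, the "Leicester Cough Questionnaire" and the mMRC scale. Section 2.2 items 3 to 6 set the scale for all four; for the last the objective is "to assess changes from baseline in the modified Medical Research Council (mMRC) Dyspnea Scale on Days 4 and 8, Week 4, and Week 12". Item 3 limits the 6MWD objective to patients who meet the second HRCT criterion of the inclusion criteria.

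Section 11.4(2), headed as the secondary efficacy evaluation, has two sentences. The first is "Proportions of individual disease progression events will be compared using chi-square" or Fisher's exact tests. The second compares times to disease recovery and symptom improvement by t-test or Wilcoxon rank-sum test.

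Section 11.4(3), on other observational indicators, analyses changes in IL-6 and then adds "Quality of life scores and total hospitalization costs will also be compared using t-tests or Wilcoxon rank-sum tests".

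Table 1 schedules 6MWD, mMRC, SGRQ and LCQ at D0, D8, D28 and D84.

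**The concern.** The endpoints declared secondary and the analysis labelled secondary are different lists. The protocol does more than omit detail: it fixes tests on other outcomes. A SAP that followed 11.4(2) would leave out the declared endpoints, and one that analysed them would depart from 11.4(2).

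Two things are at stake. First, the functional and patient-reported measures collected at four visits could go without a planned comparison, while outcomes without a definition receive tests. Second, with 24 patients and undefined terms, it could be settled after the data are seen which quantities count as secondary and on what scale they are compared.

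**Working it through.** **Step 1. Endpoints against analyses**

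| 9.1(2) endpoint | Scale in 2.2 | In 11.4(2)? | Elsewhere in section 11 |
|---|---|---|---|
| 6MWD, grade and distance | change from baseline | no | no named comparison |
| SGRQ | change from baseline | no | possibly the quality-of-life line in 11.4(3) |
| LCQ | change from baseline | no | possibly the same line |
| mMRC | change from baseline | no | no named comparison |

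Count: 0 of 4 appear in 11.4(2); at most 2 of 4 are reached in 11.4(3); 2 of 4 have no named comparison; 0 of 4 have a stated change-from-baseline or baseline-adjusted analysis. Section 11.2 supplies only general descriptive rules and the two-sided 5% level.

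**Step 2. Analyses against endpoints**

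- Individual progression events: the term is not defined. The nearest defined outcome is acute exacerbation, which is a secondary objective in 2.2 item 7 but a primary efficacy endpoint in 9.1(1) ("Frequency and severity of acute exacerbation events"). Table 1 records acute aggravating events on D1 to D8, D28, D84, D180 and D360.
- Time to disease recovery: not defined, and Table 1 has no row for it.
- Time to symptom improvement: 9.1(1) lists clinical symptoms and signs, but not as a time, and Table 1 has no row for a date of improvement.

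**Step 3. What the choice of scale could cost (illustration only)**

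The protocol justifies its 24 patients with no effect size, SD or power, so there is no planning figure to reproduce. Inputs from the protocol: 12 per arm (section 6) and two-sided 5% (section 11.2). Assumed: a true difference of 1.0 SD of the follow-up score at one visit, and a baseline to follow-up correlation r.

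Power comes from the noncentral t distribution with noncentrality d* × √(12/2):

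- score without baseline: d* = 1.0, 22 df
- simple change: d* = 1.0/√(2(1 − r)), 22 df
- baseline-adjusted: d* = 1.0/√(1 − r²), 21 df

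Without baseline, the noncentrality is 1.0 × √6 = 2.449 and power is 65%. At r = 0.3, adjustment gives d* = 1/√0.91 = 1.048, and simple change gives d* = 1/√1.4 = 0.845.

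| r (assumed) | Without baseline | Simple change | Baseline-adjusted |
|---|---|---|---|
| 0.3 | 65% | 51% | 69% |
| 0.5 | 65% | 65% | 77% |
| 0.6 | 65% | 75% | 83% |
| 0.7 | 65% | 86% | 91% |
| 0.8 | 65% | 96% | 97% |

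Simple change beats the unadjusted score only when r exceeds 0.5. The adjusted model is better than both at every r shown. All rows use 24 patients; if 6MWD is restricted as in 2.2 item 3, its sample can only be the same or smaller.

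**The case against.** **Some of the outcomes in 11.4(2) may have a basis.** If individual progression events means acute exacerbations, that item serves 2.2 item 7 and has scheduled data. Symptoms are monitored, and mMRC and LCQ are collected serially, so symptom improvement could be derived at visit resolution. This stands in part: it would be wrong to say that nothing in 11.4(2) has an objective or data behind it. But the protocol never equates the terms, and this does not bring in any of the four declared endpoints.

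**A reader might infer that SGRQ and LCQ will be tested as raw scores.** The same item speaks of changes for IL-6 and of scores for quality of life, which makes that reading plausible. The text does not establish it. The line names no instrument and does not say whether the score or its change is compared, and 2.2 items 4 and 5 already frame both as changes. The most that can be said is that the scale is unspecified.

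**Power is marginal here.** The trial is called exploratory and its primary objective is safety. That is fair. The effect size and correlations are assumptions, and the table does not measure a loss that the protocol commits to. It only supports the choice of model in the repair.

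**A SAP may settle the detail.** It may, for variable derivation. It cannot remove the conflict between 9.1(2) and 11.4(2).

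**Conclusion.** The mismatch holds on the text alone: the secondary analysis omits all four declared secondary endpoints, 6MWD and mMRC have no named comparison in section 11, and SGRQ and LCQ are at best covered by an unspecified line under a lower heading. No assumption is needed for this.

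The documents do not support two stronger readings: that SGRQ and LCQ are fixed as raw-score tests, or that every outcome in 11.4(2) is without a basis. The preference for a baseline-adjusted model is a recommendation on method, resting on the assumed values in the illustration; the gain is small at r = 0.3 (69% against 65%) and large at r = 0.8 (97% against 65%).

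The point should be corrected. It does not touch the primary safety objective. A neighbouring gap belongs to the same reconciliation: pulmonary function and HRCT are secondary objectives in 2.2 and primary efficacy endpoints in 9.1(1), and 11.4 names no comparison for them either.

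**What to change.** Rewrite 11.4(2) around the 9.1(2) endpoints:

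- **6MWD distance, SGRQ total, LCQ total:** estimate the between-group difference at one pre-named visit, for example D84, from a model with treatment and the D0 value, with a 95% CI. In choosing the visit, note that section 4.3.2 gives SGRQ Part 1 a 4-week recall and LCQ a 2-week recall, so D8 answers reach back before treatment.
- **mMRC grade and 6MWD grade:** rank-based comparison of change from D0.
- **6MWD population:** use the one stated in 2.2 item 3, or reconcile that restriction.
- **Day 4:** 2.2 items 3 to 6 call for it, but Table 1 schedules none of these four measures then; reconcile the two.
- **Events:** keep a comparison for 2.2 item 7, stated in terms of the acute exacerbations recorded in Table 1, and settle whether exacerbation is a primary or a secondary efficacy outcome.
- **Time to recovery and symptom improvement:** remove, or define from scheduled data.
- **11.4(3):** take SGRQ and LCQ out of the quality-of-life line once they are covered in 11.4(2).

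The cost is one rewritten paragraph and matching edits to 2.2, 9.1 and Table 1. All four measures and their D0 values are already scheduled, so no new data are needed unless Day 4 assessments are added. The loss is the recovery-time analysis, if it is removed.

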**2.1. Primary Objective**

To evaluate the safety of inhaled extracellular vesicle therapy in patients with pulmonary fibrotic lesions as identified by high-resolution computed tomography (HRCT).

1. to monitor vital signs, clinical symptoms and signs, and the incidence of adverse events on Days 1–8, Week 4, and Week 12 after enrollment.
2. to assess changes in laboratory and clinical parameters on Day 8 and Week 12, including complete blood count, urinalysis (plus pregnancy test), blood biochemistry, electrocardiogram (ECG), peripheral oxygen saturation (SpO₂), tumor markers, levels of IL-6 and IL-10, immune cell function in peripheral blood, and lymphocyte subsets.

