# 6. Sample Size Requirement

This study is a randomized, placebo-controlled, exploratory clinical trial. A total of 24 subjects will be enrolled at the First Affiliated Hospital of Hainan Medical University, with 12 subjects assigned to the treatment group and 12 to the placebo group.

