**12.1. Treatment Observation Period and Follow-up Methods**

Safety and efficacy observations will be conducted according to the study schedule. Additional safety follow-ups will be conducted via telephone visits at 6 and 12 months.

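### Time to symptom improvement is compared by t-test or Wilcoxon, but after Day 8 it can be observed only at Day 28 and Day 84, so a difference in mean times may be too large or too small

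*Protocol*

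**What the plan says.** Protocol Section 11.4(2), secondary efficacy: "Time to disease recovery and symptom improvement will be analyzed using grouped t-tests or Wilcoxon rank-sum tests".

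The observation times are fixed elsewhere in the protocol:

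- Section 2.1, first item: "to monitor vital signs, clinical symptoms and signs, and the incidence of adverse events on Days 1–8, Week 4, and Week 12 after enrollment". Table 1 agrees, marking vital signs and physical examination on each of D1–D8, then D28 and D84 (each ±3 days).
- The symptom instruments are sparser. After baseline, Table 1 marks mMRC, SGRQ and LCQ at D8, D28 and D84 only. Section 2.2 adds a Day 4 assessment, for example "to assess changes from baseline in the modified Medical Research Council (mMRC) Dyspnea Scale on Days 4 and 8, Week 4, and Week 12". Table 1 has no Day 4 mark for these scales, so the two places need reconciling.
- Section 12.1, on later contacts: "Additional safety follow-ups will be conducted via telephone visits at 6 and 12 months". Table 1 marks only exacerbations and adverse events at those contacts, with no symptom rating.

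Section 6 gives the size: "with 12 subjects assigned to the treatment group and 12 to the placebo group". Section 11.2 sets the tests: "All statistical tests will be two-sided" and "A p-value ≤ 0.05 will be considered statistically significant". It also says that quantitative variables are described by mean (SD) and median.

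The protocol does not define symptom improvement or mention a symptom diary or a date-of-improvement item. Section 5.3 carries forward the last major assessment of a patient who withdraws, but no rule gives a time to a patient who never improves.

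**The concern.** Both named tests take a single time per patient as if it were measured. Under this schedule the time is known to the day only up to D8. After that, all that is known is that improvement came between D8 and D28, between D28 and D84, or not by D84. If the visit day is entered as the time, two patients who improve a day or two apart can be recorded weeks apart, and two who improve weeks apart can be recorded as equal.

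Two things are at stake. One is the estimate: a difference in mean days to improvement is easy to quote, and Section 3 expects the trial to show symptom benefit. The other is power, which is already limited with 12 per arm.

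**Working it through.** **Inputs.** The visit grid (D1–D8, D28, D84) is from Section 2.1 and Table 1. The 12 per arm, two-sided testing and 0.05 level are from Sections 6 and 11.2. The protocol gives no median time, spread, effect size or power, so there is no stated figure to reproduce. All medians and log-SDs below are assumptions, shown as a range.

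**Step 1. Gaps, with no assumptions.** The gaps are 1 day up to D8, then 28 − 8 = 20 days, then 84 − 28 = 56 days. A time recorded at the first visit showing improvement behaves as follows (visit windows shift 28 and 84 by up to 3 days):

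| True days | True gap | Recorded days | Recorded gap |
|---|---|---|---|
| 27 and 29 | 2 | 28 and 84 | 56 |
| 9 and 27 | 18 | 28 and 28 | 0 |
| 29 and 83 | 54 | 84 and 84 | 0 |

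**Step 2. Difference in means.** Take lognormal times with median m and log-SD s. The chance of improving by day d is Φ(ln(d/m)/s). When almost nobody improves by D8, a recorded mean is 28p + 84(1 − p), where p is the share recorded at D28. The recorded difference between arms is then 56 × (difference in p).

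- Medians 20 vs 27, s = 0.3. True means are 20·exp(0.045) = 20.9 and 27·exp(0.045) = 28.2, a difference of 7.3. The shares are p = Φ(1.12) = 0.869 and Φ(0.12) = 0.548. Recorded difference: 56 × 0.321 = 18.0.
- Medians 35 vs 60, s = 0.3, among improvers by D84. True means are 36.5 and 57.4, a difference of 20.9. The shares are p = 0.2285/0.998 = 0.229 and 0.0055/0.869 = 0.006. Recorded difference: 56 × 0.223 = 12.5.

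Simulation over other settings, limited to patients who improve by D84:

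| Medians (days) | log-SD | True difference | Recorded difference |
|---|---|---|---|
| 5 vs 7 | 0.3–0.6 | 2.1–2.4 | 5.3–6.8 |
| 20 vs 27 | 0.3–0.6 | about 7 | 11–18 |
| 30 vs 50 | 0.5 | 14.3 | about 17 |
| 35 vs 60 | 0.5 | 14.6 | 14.3 |
| 35 vs 60 | 0.3 | about 21 | 12–13 |

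Exponential times, with patients not improved by D84 set to 84, show the same pattern: 2.9 true vs 5.5 recorded (5 vs 7), 9.8 vs 9.9 (20 vs 30) and 10.1 vs 8.3 (30 vs 45). The error can be upward, absent or downward.

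**Step 3. Tests, 12 per arm.** Under no difference (exponential times), the rejection rate on the grid stays near 0.05: t-test 0.048–0.052, Wilcoxon 0.044–0.047. Power with lognormal times, log-SD 0.5:

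| Medians | t-test, exact times | t-test, grid | Grouped-time log-rank, grid | Fisher, best single visit |
|---|---|---|---|---|
| 3 vs 5 | about 62% | about 36% | about 62% | – |
| 12 vs 20 | about 60% | 41–43% | about 43% | about 10% |
| 30 vs 50 | about 51% among improvers by D84 | about 36% | about 53% | about 27% |

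In the last row, exact times for all patients would give about 61–63%. Dropping those not improved by D84 accounts for the fall to 51%, and the grid accounts for the fall from 51% to 36%. The log-rank test keeps the dropped patients as censored.

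Wilcoxon on the grid has about 62% at 3 vs 5, the same as with exact times, and about 41% at 12 vs 20.

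**The case against.** **Most recorded times need not be set by the grid.** A reader might infer that they are. The documents do not support that, because they do not say when patients improve. Symptoms and signs are checked daily through the 7-day course, so an improvement by D8 judged on those is rounded by less than one day. This stands as a limit. It does not remove the problem: with medians of 5 vs 7 days, the later improvers alone more than double the mean difference.

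**The comparison is not invalid, nor always inflated.** A reader might infer either. Both arms share the grid, so type I error holds. The recorded difference may be too small as well as too large, and sometimes nearly right.

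**Wilcoxon is allowed.** It uses order only, so a 56-day jump does not inflate it, and for early improvement it loses nothing. For later improvement it loses power through ties, and it still has no place for a patient who never improves.

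**Some of this belongs in a SAP.** The definition of improvement and the dating rule may be set there, and the protocol does not write the word days for this endpoint. That is why the point is conditional on no onset date being collected. The test itself, however, is stated in the protocol and does not fit the protocol's own schedule.

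**The consequence is limited.** This is a secondary analysis in an exploratory trial whose primary objective is safety. That stands and sets the severity.

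**Conclusion.** The point holds as a mismatch between the stated analysis and the schedule. If times are taken from visits, any improvement after D8 is recorded as about 28 or 84. A difference in mean times is then unreliable in size and direction: about 7 true against 11–18 recorded at 20 vs 27 days, and about 21 against 12–13 at 35 vs 60 with log-SD 0.3. The grid costs the t-test roughly 15 to 20 points of power at 12 vs 20 and 30 vs 50 with log-SD 0.5.

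These sizes rest on assumed distributions and medians and on the absence of an onset date. If improvement is judged on mMRC, SGRQ or LCQ as marked in Table 1, the grid is coarser still (D8, D28, D84). A false-positive problem is not shown, and Wilcoxon is inefficient rather than wrong. Severity is low to moderate.

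**What to change.** In Section 11.4(2), replace the t-test/Wilcoxon for these times with a grouped-time (interval-censored) comparison, such as a log-rank test or a discrete-time model on the visit intervals. Record for each patient the last visit without and the first visit with improvement. Treat patients not improved at their last visit as censored there. Do not report a difference in mean days.

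Show the proportion improved by D8, D28 and D84 in each arm, with risk differences, as description only. Fisher's exact test at single visits should not be the replacement test: its power is at most about 10% (12 vs 20) and 27% (30 vs 50), and three visits would mean three tests.

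The cost is a change of wording and slightly more analysis work, with no new visits or data. The report loses a single figure for days gained. The log-rank test does not recover what the grid has lost at 12 vs 20 (about 43%, against 41–43% for the t-test). It does better at 3 vs 5 (62% vs 36%) and at 30 vs 50 (53% vs 36%).
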